##### Percentage of prescribed medication taken

Our behavioral primary outcome will be electronically monitored adherence. MEMS data will be collected continuously during the 24 months of the intervention period as well as for 12 months after the intervention ends, allowing us to investigate daily adherence and its timing. We will create a variable that captures the proportion of prescribed pills that were actually taken (i.e. number of actual bottle openings divided by the prescribed bottle openings).

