### MEMS-cap procedures

Medications will be distributed in pill bottles with MEMS caps to patients in all three groups (including the control group) at recruitment (i.e., prior to random assignment) to avoid spurious intervention effects due to the MEMS cap. These caps house a microelectronic chip that records the date and time of each bottle opening, enabling a precise and objective assessment of the timing of each dose and the patient’s pattern of pill-taking. The study coordinator will assist the patient in dispensing a supply of the medication into a bottle we provide with an attached cap, or they can simply put the MEMS cap onto the actual medication bottle if preferred by the patient. We will monitor adherence to only one antiretroviral medication as studies show that rates of adherence do not differ significantly across medications taken by an individual patient [46]. Participants will be asked to use the cap continuously throughout the study and return with the bottle and cap for each clinic visit. We will ask patients to notify the study coordinator if their provider changes their regimen during the study so that the data can be downloaded and the medication being monitored can be switched with the new one. Participants will be informed that the cap records when the bottle is opened. They will also be informed that these data will not be shared with clinicians. We will carefully discuss the restrictions associated with the electronic cap with the patient. Solutions to potential concerns that are acceptable to both the patient and the project will be provided. Once a participant has started using the cap, we will review the instructions and restrictions with the participant at each clinic visit.

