##### Estimating impact on adherence

To estimate the impact of our interventions on treatment adherence, we will use an ordinary least squares regression of the following forms:

Unadjusted:
3$$ {y}_{it}={\beta}_0+{\beta}_1T{1}_{it}+{\beta}_2T{2}_{it}+{\lambda}_t+{\epsilon}_i $$

Adjusted:
4$$ {y}_{it}={\beta}_0+{\beta}_1T{1}_{it}+{\beta}_2T{2}_{it}+{\lambda}_t+{\boldsymbol{X}}_{\boldsymbol{i}}\boldsymbol{\alpha} +{\epsilon}_i $$

where *y*_*it*_ represents the proportion of the prescribed bottle openings that were opened by individual *i* at time *t*. In this model, *β*_1_ represents the impact of T1 on the proportion of pills taken in a given month and *β*_2_ represents the impact of T2 on the proportion of pills taken in a given month. *λ*_*t*_ represents an indicator for each time period. Equation 4 includes the term ***X***_***i***_, which represents the same covariates as in Eq. 2.

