##### Estimating impact on measured adherence over time

We will have a consecutive real-time measure of adherence for the duration of the study, which allows us to study adherence over time. To estimate the impact of the interventions on adherence over time, we will use the following ordinary least squares model:
5$$ {y}_{it}={\beta}_0+\sum \limits_{t=1}^{24}{\lambda}_t\left(T{1}_{it}\times {\mathrm{Month}}_t\right)+\sum \limits_{t=2}^{24}{\delta}_t\left(T{2}_{it}\times {\mathrm{Month}}_t\right)+\sum \limits_{t=1}^{24}{\mathrm{Month}}_t+{\epsilon}_i $$

where *y*_*it*_ represents the proportion of the prescribed bottle openings that were actually opened by individual *i* in month *t*. In this model, the *λ*_*t*_’s represent the impact of T1 at study month *t* and the *δ*_*t*_’s represent the impact of T2 at study month *t*.

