### Limitations

This study has several limitations. First, the study will include only 330 patients from one clinic in Uganda. Although our sample size is well powered to detect clinically important effects, it is not clear that our results will extrapolate to other areas of Uganda or other countries. Second, while our study includes both large and small incentives, we are unable to disentangle the effect of these different incentive types and the extent to which there is a dose response with incentive size. The impact of offering different incentive types and amounts will require further research. We also cannot verify the longer-term effects of these incentives or whether any effects persist after the incentives are withdrawn beyond the 12-month period during which we will monitor the effects of the intervention. Third, although adherence is measured using MEMS caps, which is currently one of the most accurate ways to measure adherence, we cannot exclude the possibility that some participants will consciously manipulate the pill bottle openings to increase their chances of receiving the incentives. 

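### The behavioural primary outcome divides all bottle openings by prescribed openings with no limit per dosing day, which does not match the bounded proportion described for the models

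*Protocol article*

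**What the plan says.** The outcome section of the protocol article names the construct first: "We will create a variable that captures the proportion of prescribed pills that were actually taken". It then fixes the calculation, introduced as a restatement, as the "number of actual bottle openings divided by the prescribed bottle openings".

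The two model sections define the dependent variable again. For Eqs. 3 and 4, the outcome "represents the proportion of the prescribed bottle openings that were opened by individual" i at time t. For Eq. 5, it "represents the proportion of the prescribed bottle openings that were actually opened by individual" i in month t. Neither section says what happens to an opening beyond the prescribed number.

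On the device, the MEMS-cap procedures section says: "These caps house a microelectronic chip that records the date and time of each bottle opening". It also says: "Participants will be informed that the cap records when the bottle is opened". This applies to all three arms.

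Only T2 prizes depend on cap readings. T1 prizes depend on timely refills and viral suppression, and the control group has no prizes. The Limitations section concedes that it cannot rule out that "some participants will consciously manipulate the pill bottle openings to increase their chances of receiving the incentives".

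**The concern.** A total of openings divided by a total of prescribed openings is not the proportion of prescribed doses taken. It has no upper bound, and it lets a refill, a check of the bottle or any other second opening on one day stand in for a dose missed on another day. The model sections use words that fit a different quantity, the share of prescribed openings that took place, which cannot be more than 1. An analyst could follow either text and obtain different values of a primary outcome from the same cap file.

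The exposure may also be uneven. T2 participants are the only ones whose prizes turn on the cap data, so surplus openings could be more frequent there. That would affect T2 against control and T2 against T1, and the second contrast is the trial's main implementation question. The secondary outcome of taking at least 90% of pills would share the problem if it is derived from the same ratio.

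**Working it through.** **1. The plan's own yardstick.** Sample size and power gives detectable differences in mean adherence of 6.5 points (T1 and T2 combined against control) and 7.5 points (T1 against T2) at month 12, and 7 and 8 points at month 24. No standard deviation is stated, so these cannot be reproduced directly. They can be checked for consistency with MDE = (1.960 + 0.842) × SD × √(1/n₁ + 1/n₂). The inputs are 80% power, two-sided alpha 0.05 (assumed), 110 per arm and 10% attrition a year, giving 99 per arm at month 12 and 89.1 at month 24.

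| Comparison | Stated MDE | Implied SD | MDE at SD 19 |
|---|---|---|---|
| Combined vs control, month 12 | 6.5 | 18.8 | 6.6 |
| T1 vs T2, month 12 | 7.5 | 18.8 | 7.6 |
| Combined vs control, month 24 | 7 | 19.3 | 6.9 |
| T1 vs T2, month 24 | 8 | 19.1 | 8.0 |

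All four agree with one SD of about 19 points. They are not in dispute and serve only as a scale.

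**2. The two definitions on the same data.** Let p be the share of prescribed occasions with an opening and e the surplus openings per prescribed opening. The stated formula gives p + e; the bounded reading gives p. For 30 once-daily days, with 24 opened, 6 missed and 6 surplus openings:
- stated formula: (24 + 6)/30 = 100%
- bounded proportion: 24/30 = 80%

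**3. Illustration of size.** The rate of surplus openings is an assumption; the article gives none. For one extra opening per 14 days:
- once-daily: 1/14 = 7.1 points for that client
- twice-daily: 1/28 = 3.6 points for that client

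If one third of T2 clients did this and nobody in T1 or control did:
- T2 mean, once-daily: 7.1/3 = 2.4 points
- T2 mean, twice-daily: 3.6/3 = 1.2 points

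The relevant yardstick for these is the T1 against T2 figure of 7.5 to 8 points. In the combined comparison, with T1 and T2 of equal size, the shift is halved to about 1.2 or 0.6 points, against 6.5 to 7.

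**4. What such a shift would do to a test.** With no true effect, 99 per arm, SD 19 and two-sided 0.05, a spurious difference of 1 point gives a rejection probability of about 7%, and 2.5 points about 15%.

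**5. The opposite direction.** The T2 section on prize draws at clinic visits reports that about 15% of an earlier sample pocketed doses, which lowers recorded openings. If those 15% were on twice-daily dosing and pocketed one of the two doses on a quarter of days (assumed), the mean would fall by 0.15 × 0.25 × 0.5 = 1.9 points. That is of the same order as step 3, with the opposite sign.

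**The case against.** The strongest reply is that the bounded definition is already in the article. The named construct is a proportion of pills, and both model sections read as bounded. The article also plans to look at daily adherence and screens participants on the share of days with an opening. On that view the formula is a loose parenthesis, and the handling of surplus cap events belongs in the full protocol or analysis plan. This softens the point but does not remove it. The formula is stated, it is the only calculation rule given for a primary outcome, and taken literally it yields a different quantity.

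A reader might infer more: that T2 is rewarded for extra openings, so its effect will be inflated by about the size the trial is planned to detect. The article does not support this, for five reasons.
- T2 eligibility is worded by occasions on which medication was due. Under that wording a second opening on a day already covered earns nothing.
- No rate of surplus openings is given for any arm. Refill and checking openings can occur in all three and would tend to cancel in contrasts.
- The 7.1 points is one once-daily client's inflation and is not comparable with a difference in arm means. The article also describes clients with morning and evening doses.
- Pocketing lowers measured adherence, and its balance across arms is unknown. The adjustment described for it concerns T2 prize eligibility only, not the outcome.
- The 90% secondary outcome is described in terms of pills taken, without a formula. Misclassification there is conditional on its using the same ratio.

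It also stands that a daily limit cannot detect a sham opening on a missed occasion. Viral suppression, the other primary outcome, does not depend on openings.

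**Conclusion.** The point holds as a fault in the outcome definition. The stated formula can exceed 1, lets surplus openings offset missed doses, and does not agree with the bounded wording used for Eqs. 3 to 5. That follows from the text and simple arithmetic, with no assumption about behaviour.

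Differential bias in T2 is possible but unquantified, and neither its size nor its net direction can be fixed from the article. The illustrative shift of 1.2 to 2.4 points in the T2 mean rests on an assumed rate of one surplus opening per 14 days, in one third of T2 clients, with none in the other arms. It is well below the planned detectable differences, though large enough to disturb the type I error if it occurred.

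**What to change.** In all arms, count openings on each dosing day only up to the number prescribed for that day, sum them over the period, and divide by the prescribed openings over the same period. Use this one definition in the outcome section, in Eqs. 3 to 5 and for the 90% secondary outcome. Report the uncapped ratio and the rate of excess openings by arm as a sensitivity analysis; this would also show whether the arms differ.

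The cost is a sentence in the definition and a small change in the code, since the caps already log the date and time of each opening. Measured adherence will be slightly lower. The boundary of the dosing day also needs stating, because an opening shortly after midnight could otherwise count as both a miss and a surplus. The change does not address sham openings on missed occasions, which should remain as the limitation the article already states.

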### Sample size and power

We have calculated the size of effects that our sample will be able to detect with 80% power (two-tailed test) with regard to outcomes at months 12 and 24, and 10% attrition every year (we observed 5% attrition over 20 months in our previous studies so this is a conservative estimate). For the primary outcome of viral suppression, we use a conservative estimate of 70% of clients in the control group showing suppression, based on discussions with the Mildmay team. Our sample size of 110 participants in each of the three arms (total *n* = 330) will be able to detect a 7 percentage point difference for joint comparison of T1 and T2 against the control group at month 12, and about an 8.5 percentage point difference between the two intervention arms (a subgroup analysis). The corresponding differences at month 24 are 8 and 9 percentage points, respectively. These are considered small effect sizes (Cohen’s *d* of between .15 and .185), which we will be able to detect. For adherence, in our previous study we observed mean adherence rates of ~75% as measured by MEMS caps. Our sample size of 110 in each of the intervention arms and the control group will provide sufficient power to detect about a 6.5 percentage point difference in mean adherence between the two intervention arms (combined) and the control group. To test for differences in adherence between the two intervention arms, our study is powered to detect about a 7.5 percentage point effect as measured by MEMS caps. Again, this means we will be able to detect small effects. The corresponding differences we will be able to detect at month 24 are about 7 and 8 percentage points, respectively. Our main econometric models will include covariates that will improve precision. Therefore, these minimum detectable effects reported above are likely upper bounds.

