## Background

Treatment adherence is critical to the success of antiretroviral treatment (ART) and is largely determined by behavior. Over 1.3 million Ugandans are infected with HIV and prevalence is still over 6% [1]. ART has improved the life expectancy of people living with HIV/AIDS in Uganda dramatically, and a scaling up of treatment has resulted in over 72% of these Ugandans receiving ART [2–8]. Yet the success of these drugs is dependent on high *lifelong* medication adherence to achieve optimal clinical outcomes, such as slowing the progression to AIDS, lengthening survival, sustained viral suppression, and prevention of drug resistance and loss of treatment options [9–14]. Moreover, ART adherence in Uganda may be lower than previously assumed [15] and be declining over time [16, 17]. Both structural (e.g., drug availability) and practical (e.g., distance to clinic and treatment fees) adherence barriers have been investigated [18–20], yet patient behavior has emerged as a key factor for adherence [21].

Newer, simpler regimens are also plagued by low adherence, and are often not available in resource-poor countries. These ART regimens are more forgiving [22–24], but result in only marginally better adherence [25]. Adherence remains key to the success of ART [26–28], and at least 80–85% adherence is needed to sustain viral suppression and prevent drug resistance [22–24]. Despite the importance of adherence and simpler regimens, mean ART dose-taking adherence (percentage of prescribed doses taken) typically ranges from 60 to 80% when measured electronically, and only 30–60% of patients achieve 85% adherence [29–31]. In addition, these simpler regimens are often not available in sub-Saharan Africa and other resource-constrained environments.

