### Inclusion criteria

Our study sample will be 330 HIV patients aged 18 and older who have been on ART at Mildmay for 2 years or longer to filter out clients who are at Mildmay only transiently and to target treatment-mature clients for whom it is likely that the motivational problems that are the target of our intervention are a significant barrier to adherence. They must have had recent adherence problems within the past 6 months based on clinical records (defined as showing lack of viral suppression, being sent to adherence counseling, or at disease stage 3 or 4 as per WHO guidelines). Our decision to enroll patients with adherence problems is based on our conceptual framework, which suggests that motivation is a key driver of adherence in treatment-mature HIV clients, as well as on meta-analysis data showing that HIV adherence interventions have a larger effect size for such clients (mean effect size 0.62) compared to effects on interventions applied to all patients (mean effect size 0.19), in general [44].

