### Randomization

Randomization in a 1:1:1 ratio will occur after participants are recruited but before they complete a baseline survey to ensure that group assignment does not influence the answers given. We will stratify random assignment by age (under 25 or over 25), sex, marital status (married/cohabiting or unmarried), low CD4 count (below 200 or above 200), and viral load (detectable or undetectable). Stratified randomization is achieved by generating a separate block for each combination of covariates after identifying which clients fall into each block. We will then randomize treatment assignment within each block. We will use the *randtreat* package in Stata15 for the randomization procedure.

All clients recruited will complete the baseline survey approximately 2–3 months after recruitment. The client will be informed of their assignment to either one of the two intervention arms or the control group after completing the baseline survey.

Participants cannot be blinded to their treatment status and neither can interviewers. Interviewers are not blinded to treatment status when they read a MEMS cap. The data analyst who will conduct the impact analysis will be blinded to treatment assignment.

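### The 70% control suppression rate is called conservative without support, and the suppression detectable differences should be recomputed over a range of control rates

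*Protocol article*

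**What the plan says.** The Sample size and power section sets the control rate for viral suppression as follows: "we use a conservative estimate of 70% of clients in the control group showing suppression, based on discussions with the Mildmay team". It reports detectable differences "with 80% power (two-tailed test) with regard to outcomes at months 12 and 24, and 10% attrition every year", with 110 participants per arm. For the two intervention arms pooled against control these are 7 percentage points at month 12 and 8 at month 24.

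Three other statements bear on the control rate:

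- Inclusion criteria, on who may enter: "They must have had recent adherence problems within the past 6 months based on clinical records". Lack of viral suppression is one of three alternative ways to qualify. The others are referral to adherence counseling and WHO stage 3 or 4.
- Background, on adherence and suppression: "at least 80–85% adherence is needed to sustain viral suppression and prevent drug resistance", and "only 30–60% of patients achieve 85% adherence".
- Sample size and power again: mean MEMS adherence in the team's previous study was about 75%.

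No section reports an observed suppression rate for clients who meet the inclusion criteria.

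**The concern.** A planning rate is conservative if the truth is likely to be kinder to the design. The protocol sizes on percentage points and its analysis section names the risk difference as the contrast. On that scale the variance of a proportion grows as the rate moves from 70% towards 50%. So 70% is the safe choice only if controls do better than 70%. The only stated basis is discussion with the clinic team, while the article's own material on adherence points, if anything, the other way.

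The control rate enters every suppression power figure. The Limitations section tells the reader that the sample has good power for effects that matter clinically. If the rate is lower than planned, the trial detects only larger differences than even a correct calculation at 70% would show, and a null result on suppression could be read as stronger evidence than it is.

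**Working it through.** **Inputs.** Control rate 70%, 80% power, two-tailed test, 10% attrition a year and 110 per arm (Sample size and power); 1:1:1 allocation (Randomization). The significance level is not stated, so two-sided 5% is assumed. Participants remaining per arm: 110 × 0.9 = 99 at month 12 and 110 × 0.81 = 89.1 at month 24. Pooled intervention against control is therefore 99 vs 198 and about 89 vs 178.

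**Formula.** With control rate p0, intervention rate p1 = p0 + d, and overall rate p̄ weighted by arm size:

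- s0 = √[p̄(1 − p̄)(1/n0 + 1/n1)]
- s1 = √[p0(1 − p0)/n0 + p1(1 − p1)/n1]
- power = Φ[(d − 1.96·s0)/s1]

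**Step 1: the stated figure.** For p0 = 0.70 and d = 0.07: p̄ = (99 × 0.70 + 198 × 0.77)/297 = 0.7467, s0 = 0.05353, s1 = 0.05491. Then (0.07 − 1.96 × 0.05353)/0.05491 = −0.636, so power is 26.2%, not 80%. The stated 7 points does not reproduce. Dropping attrition, using a 10% level or using a one-sided test does not rescue it: the smallest pooled detectable difference among the variants tried (one-sided 10%, no attrition) is 10.6 points.

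**Step 2: the detectable difference at 70%.** Solving for 80% power gives d = 0.1419. Check: p̄ = 0.7946, s0 = 0.04973, s1 = 0.05285, and (0.1419 − 1.96 × 0.04973)/0.05285 = 0.84, which gives 80%.

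**Step 3: other control rates, pooled intervention against control.**

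| Control rate | Detectable difference, month 12 | Detectable difference, month 24 | Power for 7 points, month 12 |
|---|---|---|---|
| 40% | 17.2 | 18.1 | 20.5% |
| 50% | 16.8 | 17.7 | 20.7% |
| 60% | 15.9 | 16.6 | 22.3% |
| 70% | 14.2 | 14.9 | 26.2% |
| 80% | 11.7 | 12.2 | 35.9% |
| Protocol, at 70% | 7 | 8 | 80% (claimed) |

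At month 12, moving from 70% down to 60%–40% adds 15.9 − 14.2 = 1.7 to 17.2 − 14.2 = 3.0 points. Moving up to 80% removes 14.2 − 11.7 = 2.5 points. The direction therefore turns on a rate the document does not report.

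**Step 4: what the document says about that rate.** The rates of 40–60% and 80% are assumptions used to show a range. On one side stand selection for recent adherence problems, the 80–85% adherence said to be needed for suppression, and mean adherence of about 75%. On the other stand the three alternative entry routes, stratification by detectable or undetectable viral load (so suppressed clients are expected to enter), and exclusion of clients who opened the cap on fewer than 30% of days.

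**The case against.** **The documents do not show that 70% is wrong.** This stands. A client can qualify through counseling referral or disease stage while suppressed. The adherence problem lies in the six months before entry, whereas the outcome is read at months 12 and 24, and controls can still be referred for counseling. The 30–60% range is background literature, not this clinic. Reading suppression off cap data is also unsafe: the protocol says factors other than adherence affect viral load, and that pocketed doses, reported by about 15% of an earlier sample, appear as missed. A reader might infer that true control suppression is 40–60%. The documents raise that possibility and do not establish it.

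**The loss of power is not a fixed quantity.** This also stands. A reader might infer that a lower control rate costs 10 to 16 points of power. That holds only if a 14.2-point absolute difference is kept constant (80% power at 70%, then 70%, 65% and 64% at 60%, 50% and 40%), and the protocol never states such a difference. At its stated 7 points, power goes from 26% to 21–22%. At a fixed odds ratio of 2.28 (70% to 84.2%), power rises to 87%, 91% and 92%. Because the protocol sizes and reports in percentage points, the absolute scale is the relevant one, but the claim should be about detectable differences.

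**The arithmetic error is larger.** True: 14.2 − 7 = 7.2 points, against 1.7 to 3.0 from the control rate. But correcting the arithmetic at 70% would still leave an input with no data behind it and an unsupported label.

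**Covariates will help.** The protocol calls its differences likely upper bounds for this reason. A 7-point difference needs about 462 controls, so covariates would have to remove 1 − 99/462 = 79% of the variance.

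**Conclusion.** The concern holds in a limited form. Calling 70% conservative is unsupported: for a fixed percentage-point difference it is true only if control suppression exceeds 70%. The article gives no rate for the enrolled group, and its own adherence figures leave room for a lower one. The month-12 detectable difference for pooled intervention against control is 14.2 points at 70%, and runs from 11.7 at 80% to 17.2 at 40%. At month 24 it is 14.9 at 70%, and runs from 12.2 to 18.1. None of these is near the stated 7 and 8.

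This rests on an assumed two-sided 5% level, the stated attrition, an unadjusted two-proportion test, and control rates other than 70% that are illustrative. It does not show that 70% is too high.

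**What to change.** In the Sample size and power section:

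1. Replace the discussion-based rate with suppression below 200 copies/mL in the clinic's electronic records among clients who meet the inclusion criteria, or with the baseline viral loads of those enrolled so far, pooled over arms. Baseline status is only a guide to the month-12 and month-24 control rates, which is a further reason to show a range.
2. Drop the word conservative unless that rate is above 70%.
3. Restate the suppression detectable differences, correctly computed and with the significance level given, over control rates such as 50–80%: 16.8 to 11.7 points at month 12 and 17.7 to 12.2 at month 24 for the pooled comparison. Recompute the comparison between the two intervention arms in the same way.

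Keep the sample size. The cost is one query of a database already used to find eligible clients, plus a short edit. The downside is that the stated detectable differences become less favourable.
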